#### 5.6.7. Other Measures

- **The 8 item version of Client Satisfaction Questionnaire (CSQ-8):** The CSQ is a commonly used questionnaire for assessing satisfaction with psychotherapy services. While the original CSQ consists of 18 items, the 8-item version of CSQ (CSQ-8) has also demonstrated high internal consistency, and satisfaction scores measured by these scales have been shown to predict positive outcomes. The reliability and validity of the Japanese version of the CSQ-8 have been established.
- **The Working Alliance Inventory-Short Form (WAI-SF):** The WAI-SF is a 12-item measure that assesses the strength of the bond between the patient and therapist, as well as the degree of agreement on treatment goals and content. Each item is rated on a 7-point Likert scale. The total WAI-SF score ranges from 12 to 84, with higher scores indicating a stronger therapeutic alliance. The Japanese version of the WAI-SF has demonstrated good reliability and validity.

## 6. Planned Statistical Analysis

Statistical analyses will be performed using SPSS Statistics software (version 29; IBM Corp) or R Statistics.

Analyses will be conducted based on the intention-to-treat principle (ITT), in accordance with the CONSORT

2010 checklist. All *P*-values will be two-tailed, and a *P*-value < .05 will be considered statistically significant.

### **6.1. Primary Confirmatory Analyses**

The primary indicator for evaluating the effectiveness of the intervention will be whether the difference between the intervention and control groups at 12 weeks is statistically and clinically significant. The primary outcome will be analyzed as the total number of binge eating and purging episodes. A mixed linear model (MLM) will be constructed to examine the effects of time, group (intervention or control), and their interaction. The treatment effect will be calculated as a standardized effect size using Cohen's *d* and will also be presented as the least squares mean difference estimate with a 95% confidence interval (95% CI).

The protocol originally specified analysis of covariance (ANCOVA) as the primary analysis method, as outlined in the published protocol paper. However, to better align with the evolving understanding of data characteristics and to enhance analytical precision, we updated the protocol and adopted linear mixed models (LMM) as the primary analysis method, following recommendations from prior studies. Analysis of covariance (ANCOVA) will be reported as a sensitivity analysis.

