#### **5.6.3. Primary Outcome**

The primary outcome, the weekly combined frequency of binge eating and compensatory behavior episodes, is assessed at baseline and 12 weeks post-intervention. The independent assessor team at the University of Fukui measures the primary outcome via telephone.

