## **6.6. Sample Size Calculation**

The target sample size for this study is set at 60 participants, with 30 participants in each group. The rationale for this sample size was determined using the statistical analysis software G\*Power 3.1, based on a calculation for an independent t-test. The effect size (Cohen's  $d = 0.9$ ) was derived from a previous study on ICBT for bulimia nervosa, which reported significant reductions in the frequency of binge eating and purging behaviors compared to the waitlist group. Assuming an expected effect size of 0.9 for this study, with a significance level of 0.05 (two-tailed) and a power of 80% ( $1-\beta$ ), a minimum of 21 participants per group is required.

To account for a dropout rate of 30%, an additional 9 participants per group are anticipated, bringing the required sample size to 30 participants per group. Therefore, the total target sample size for the study is 60 participants. This ensures sufficient power to detect significant differences between the intervention and control groups.

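### With two time points, the primary mixed model does not adjust for baseline and is less precise than the ANCOVA it replaced; the plan also names two different contrasts

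*Protocol*

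**What the plan says.** Section 5.6.3 states that the primary outcome, the weekly combined frequency of binge and compensatory episodes, "is assessed at baseline and 12 weeks post-intervention". No intermediate assessment of it is described.

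Section 6.1 defines the primary indicator as "whether the difference between the intervention and control groups at 12 weeks is statistically and clinically significant". It then gives the model: "A mixed linear model (MLM) will be constructed to examine the effects of time, group (intervention or control), and their interaction". The effect is to be reported as Cohen's d and as a least squares mean difference with a 95% confidence interval. No baseline covariate and no common-baseline constraint is stated. The same section explains that ANCOVA was the method first specified, that the mixed model replaced it partly for better precision, and that ANCOVA is now a sensitivity analysis. Section 6.2 applies the same model to the secondary outcomes.

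Section 6.6 sizes the trial "based on a calculation for an independent t-test", at two-sided 5% significance and 80% power. It uses d = 0.9 and concludes that "a minimum of 21 participants per group is required", raised to 30 per group for 30% dropout. No calculation for the mixed model and no baseline to week-12 correlation is given.

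**The concern.** A mixed model gains over simpler methods when there are several follow-up visits, or when it borrows strength from the baseline. Here there is one follow-up visit, and two arms by two occasions give four means. Main effects plus interaction use four parameters, so the model fits all four means freely. Baseline then enters the treatment effect either with a fixed coefficient of one (the interaction) or, on complete data, not at all (the week-12 difference). ANCOVA estimates the coefficient that minimises the residual variance.

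Two things are at stake. The change of primary method gives up precision while claiming to gain it, in a trial planned on 21 evaluable participants per arm, and section 6.2 carries this to the secondary outcomes. In addition, section 6.1 points both to the week-12 difference and to the interaction. In this model these are different estimates with different p-values, so the primary test is not uniquely fixed.

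**Working it through.** **Inputs.** From section 6.6: d = 0.9, two-sided alpha 0.05, 80% power, 21 evaluable and 30 randomised per arm. From section 5.6.3: two occasions. Assumptions: rho is not in the protocol, so a range is shown; equal variances at both occasions; d = 0.9 in units of the week-12 SD; ANCOVA taken with baseline as covariate.

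**The plan's own figure.** The noncentrality of the independent t-test with n per arm is d × sqrt(n/2). At n = 21 this is 0.9 × sqrt(10.5) = 2.92 on 40 degrees of freedom, giving power 0.812. At n = 20 power is 0.792. So 21 is reproduced, and 21/0.70 = 30.

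**What the model estimates.** The model was fitted to simulated complete two-occasion data with 30 per arm. At rho 0.5 the interaction was -0.9299 (SE 0.2614), and the difference in mean change was also -0.9299 (SE 0.2614). At rho 0.3 both were -0.7526 (SE 0.2534). Multiple imputation (section 6.4) does not alter this, because each imputed data set is complete.

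**Precision.** Write s0 and s1 for the SDs at baseline and week 12. Per participant:

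- ANCOVA: s1²(1 - rho²)
- change score: s0² + s1² - 2·rho·s0·s1 = s1²(1 - rho²) + (s0 - rho·s1)²
- raw week-12 score: s1²

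The added square is never negative, so the change score cannot be expected to beat ANCOVA whatever the two SDs. With s0 = s1 the ratios to ANCOVA are 2/(1+rho) for the interaction and 1/(1 - rho²) for the week-12 difference:

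| rho | interaction / ANCOVA | week-12 difference / ANCOVA |
|---|---|---|
| 0.3 | 1.54 | 1.10 |
| 0.5 | 1.33 | 1.33 |
| 0.7 | 1.18 | 1.96 |

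These are expected ratios; a single small sample can depart from them.

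**Power with 21 complete pairs per arm.** The effective effect size is 0.9/sqrt(2(1 - rho)) for the interaction (40 df) and 0.9/sqrt(1 - rho²) for ANCOVA (39 df). At rho 0.3 these are 0.9/1.183 = 0.761 and 0.9/0.954 = 0.943.

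| rho | interaction | week-12 difference | ANCOVA |
|---|---|---|---|
| 0.2 | 0.614 | 0.812 | 0.827 |
| 0.3 | 0.672 | 0.812 | 0.846 |
| 0.4 | 0.738 | 0.812 | 0.873 |
| 0.5 | 0.812 | 0.812 | 0.907 |
| 0.6 | 0.889 | 0.812 | 0.945 |
| 0.7 | 0.957 | 0.812 | 0.978 |

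**Where the interaction test crosses 80%.**

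- 21 complete pairs per arm: rho = 0.484.
- All 30 baselines and 21 week-12 values per arm, with variance per arm (1 - rho²)/21 + (1 - rho)²/30: power 0.720, 0.777 and 0.841 at rho 0.3, 0.4 and 0.5; crossing at rho = 0.437.
- No dropout, 30 pairs per arm: crossing at rho = 0.252.

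With all 30 baselines, the week-12 contrast has variance per arm (1 - rho²)/21 + rho²/30 and power 0.817 to 0.869 for rho 0.2 to 0.7.

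**Evaluable participants per arm for 80% power.** The interaction needs 29, 25 and 21 at rho 0.3, 0.4 and 0.5; ANCOVA needs 19, 18 and 16.

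**The case against.** The strongest reply is that section 6.1 opens by naming the group difference at 12 weeks and reports it as a least squares mean difference. On that reading power stays at about 81% at any rho. The effect size is also undefined: "Assuming an expected effect size of 0.9 for this study" does not say whether the SD is that of week-12 or change scores. If it is that of change scores, 21 per arm already gives the interaction 81%. Both points stand. A reader might infer that the trial misses its stated power, or does so whenever rho is below 0.5. The protocol supports neither: rho 0.5 is where the interaction merely equals the planned t-test, and the 80% line lies lower.

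A reader might also infer a biased result or an inflated type I error. Under randomisation either contrast, if fixed in advance, is unbiased and holds its nominal level, and nothing in the protocol allows success on whichever contrast is significant. The defect is lost efficiency and an unnamed contrast.

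It can be said that covariance structure and contrast statements belong in an analysis plan that is not shown, and that section 6.1 does not forbid baseline adjustment. That would answer a complaint about missing detail. It does not answer this one, since the protocol itself names the model terms and gives a reason for the switch that the model does not bear out. Lastly, section 9 dates completion of the analysis at 30 December 2024, so a change is not a mere edit before data. But ANCOVA was the method first specified and is still planned, so restoring it introduces no new analysis.

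**Conclusion.** The point holds as one of efficiency and specification. With two occasions, the model as written gives a change-score test or, on complete data, an unadjusted post-score comparison. Under equal variances both are less precise than ANCOVA for rho strictly between 0 and 1. The interaction's variance is 18% to 54% larger over rho 0.7 to 0.3, and the precision rationale in section 6.1 is the wrong way round.

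The effect on power is conditional. If the interaction is primary and d = 0.9 is in week-12 SD units, power is below 80% when rho is under about 0.48 with 21 pairs per arm, about 0.44 if all 30 baselines are used, and about 0.25 with no dropout. If the week-12 difference is primary, the stated power is met but remains below that of ANCOVA for rho above 0. The protocol settles none of the contrast, the SD behind d, or rho. ANCOVA with 21 evaluable per arm has at least 0.81 power at every rho under the same assumptions.

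**What to change.** Choose one of two equivalent routes:

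- Make ANCOVA primary, with the week-12 value regressed on group and baseline, and state baseline explicitly as the covariate.
- Keep a mixed model but give both arms one baseline mean: time plus group-by-time, no group main effect, unstructured 2×2 covariance. The interaction and the week-12 difference are then the same baseline-adjusted estimate.

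In either case, name that estimate as the single primary contrast, use the same form for the secondary outcomes in section 6.2, correct the precision rationale in section 6.1, and state in section 6.6 which SD d = 0.9 refers to.

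No new data or participants are needed. The cost is a further change of primary model, which must be dated and justified openly given the timeline in section 9. Keeping the current mixed model as a sensitivity analysis lets readers see both results.

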### **6.2. Secondary Confirmatory Analyses**

Secondary analyses will be conducted using the same statistical model as the primary analysis to evaluate the multifaceted effects of the intervention through secondary outcomes (eating disorder severity, depression,

anxiety, and quality of life). The analyses will examine differences between groups as well as changes over time.

### **6.3. Exploratory Analyses and Additional Statistical Tests**

To assess treatment satisfaction and therapeutic alliance, the post-treatment mean values will be calculated for the intervention group. To evaluate baseline differences between the two groups, independent samples t-tests, chi-square tests, and Fisher's exact tests will be used. For the binary outcome of remission in bulimia nervosa (BN), a chi-square test will be employed to assess the significance of the odds ratio (OR). The criteria for remission will be determined using the cutoff values of the EDE-Q score, 2.34 or 2.80.

### **6.4. Missing Data and Sensitivity Analyses**

Missing data will be imputed using Multiple Imputation by Chained Equations (MICE). For sensitivity analyses, the difference in mean change scores from baseline to 3 months between the two groups will be examined using analysis of covariance (ANCOVA) to determine statistical significance. Additionally, observed power will be calculated to assess the validity of the primary results. A per-protocol set (PPS) analysis will also be conducted by excluding patients who deviated from the study protocol.

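### Section 6.4 judges the validity of the primary result by observed power, which only restates the p-value

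*Protocol*

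**What the plan says.** Section 6.4 names multiple imputation by chained equations for missing data and then lists three further items:

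- an ANCOVA on the change from baseline to 3 months;
- observed power, with its purpose stated: "observed power will be calculated to assess the validity of the primary results";
- a per-protocol analysis: "A per-protocol set (PPS) analysis will also be conducted by excluding patients who deviated from the study protocol".

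Section 6.1 makes a linear mixed model with time, group and their interaction the primary analysis. It reports the least squares mean difference with a 95% confidence interval and Cohen's d, and also names ANCOVA as a sensitivity analysis. Section 6 sets significance at a two-tailed p below .05. According to Section 5.6.3, the primary outcome "is assessed at baseline and 12 weeks post-intervention", with no interim measurement mentioned. Section 6.6 plans on d = 0.9, 80% power and two-tailed alpha of 0.05, giving 21 per group, raised to 30 per group for 30% dropout.

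**The concern.** Observed power is the power the test would have if the true effect equalled the estimate just obtained. Its inputs are the test statistic and the sample size, and these already determine the p-value. A number derived from the same statistic cannot serve as an independent check on it.

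The practical risk lies in interpretation. A result just under p = 0.05 would be described as having about 50% power, which sounds like a weakness in the design. A non-significant result would always have observed power below or around 50%, which invites the explanation that the trial was too small, even when the confidence interval excludes the planned effect. A very small p-value would appear to be confirmed by high power when nothing has been confirmed.

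There is a secondary point. This statistic occupies a place in a section on missing data and sensitivity analyses where a more useful check could stand. The two other listed analyses do not examine what happens if missing outcomes differ systematically from those imputed.

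**Working it through.** **1. The plan's own figures.** Inputs from Section 6.6: d = 0.9, alpha = 0.05 two-tailed, power 80%, 30% dropout. For a two-sample t-test with n per group, df = 2n − 2 and the noncentrality is d × √(n/2). Power is 79.2% at n = 20 and 81.2% at n = 21, so 21 per group reproduces. Dropout: 21 / (1 − 0.30) = 30 per group, which also reproduces. No sample-size figure is disputed.

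**2. Observed power as a function of p.** For a given p, the observed statistic is t_obs = t(1 − p/2; df) and the observed effect is d_obs = t_obs × √(2/n). Observed power sets the noncentrality equal to t_obs:

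power = P(T′ > t_crit) + P(T′ < −t_crit), where T′ is noncentral t with df = 2n − 2 and noncentrality t_obs.

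| p-value | d_obs, n = 21 | observed power, n = 21 | d_obs, n = 30 | observed power, n = 30 |
|---|---|---|---|---|
| 0.001 | 1.096 | 93.4% | 0.895 | 92.6% |
| 0.01 | 0.835 | 75.1% | 0.688 | 74.5% |
| 0.05 | 0.624 | 50.5% | 0.517 | 50.3% |
| 0.10 | 0.520 | 37.6% | 0.432 | 37.6% |
| 0.20 | 0.402 | 24.6% | 0.335 | 24.7% |
| 0.50 | 0.210 | 10.2% | 0.175 | 10.2% |

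Once p is known, observed power is known to within a percentage point, whichever sample size applies. At p = 0.05 the observed statistic equals the critical value, which is why the result is about 50%. With a mixed model and pooled imputations the degrees of freedom vary, so the link is near-exact rather than exact.

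**3. What the confidence interval shows and observed power does not.** Take p = 0.20 at both sample sizes. In observed SD units the 95% half-width equals the smallest significant d: 0.624 at n = 21 and 0.517 at n = 30.

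- n = 21: 0.402 ± 0.624 = −0.22 to 1.03, which includes the planned 0.9.
- n = 30: 0.335 ± 0.517 = −0.18 to 0.85, which excludes the planned 0.9.

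Observed power is about 25% in both cases. The interval separates a result compatible with the planned effect from one that is not.

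**4. Illustration of a departure from missing at random.** The only input from the protocol is the 30% allowance. It is assumed here that 30% of ICBT 12-week outcomes are missing and are worse than imputed by δ SD. The protocol gives no δ. The mean difference becomes 0.9 − 0.3 × δ.

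| δ (SD) | difference (original SD units) |
|---|---|
| 0.3 | 0.81 |
| 0.6 | 0.72 |
| 0.9 (no benefit in those patients) | 0.63 |
| 1.2 | 0.54 |

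These are mean differences in original SD units. In the no-benefit case, mixing two patient groups raises the ICBT-arm variance to 1 + 0.7 × 0.3 × 0.9² = 1.17. The pooled SD is √((1.17 + 1)/2) = 1.04, and Cohen's d is 0.63 / 1.04, or about 0.60.

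**The case against.** The strongest reply is that nothing depends on observed power. Section 6.4 attaches no threshold or action to it. Inference rests on the two-tailed p-value and on the mean difference with its interval, so deleting the sentence changes no estimate, test or decision. This stands and limits the harm to a misleading supplementary statement. It does not rescue the sentence, because the protocol states the purpose as well as the calculation, and the calculation cannot serve that purpose. No analysis plan held elsewhere would change this.

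The missing-data side invites stronger readings that the document does not support.

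- A reader might infer that the plan fails by not testing missing at random. That assumption cannot be tested from the observed data; one can only examine departures from it. Such an analysis could also sit in a statistical analysis plan not shown, and Section 6.4 does not call its list exhaustive.
- A reader might infer that the sponsor expects 30% informative loss in the ICBT arm. Section 6.6 gives a planning allowance applied equally to both groups. Outcomes are collected by telephone by an independent team (Section 5.6.3), analysis is by intention to treat (Section 6), and the stipend is the same in both arms (Sections 5.3 and 8.3). A patient who stops the modules may still give an outcome.
- A reader might take 0.63 as the expected effect. It is one scenario within an assumed range.

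What remains is narrower. ANCOVA changes the model but not the assumption about missing outcomes, and the per-protocol set selects on adherence. With measurement only at baseline and 12 weeks, a patient lost before week 12 has no interim value of the primary outcome to inform the imputation.

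**Conclusion.** The point holds for observed power. As a stated check of validity it is wrong, because it repeats the p-value: about 25%, 50%, 75% and 93% at p = 0.20, 0.05, 0.01 and 0.001, for 21 or 30 per group alike. This rests on a two-sample t-test and is near-exact for the planned mixed model. The consequence is a potentially misleading interpretation, not a wrong primary estimate or test.

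The missing-data part is a recommendation and not a demonstrated defect. The range of 0.81 to 0.54 SD shows only that departures from missing at random could matter at the planned dropout allowance; both the shift and its restriction to the ICBT arm are assumptions.

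**What to change.** Delete the observed-power sentence from Section 6.4. State instead that precision, and compatibility with the planned 0.9 SD effect, will be judged from the mean difference and 95% confidence interval in Section 6.1. This costs nothing.

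Optionally, use the freed place for one sensitivity analysis of departures from missing at random, for example control-based or delta-adjusted imputation of missing ICBT-arm 12-week outcomes, and report whether the conclusion changes. This needs a modified imputation specification, so it is a modest amount of extra work beyond the planned imputation, and the estimate may be less favourable.

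Section 9 dates completion of the analysis to December 30, 2024. If the analysis is already done, the change applies to reporting: do not offer observed power as evidence of validity, and label any added missing-data analysis post hoc.

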### **6.5. Assessment of Blinding**

To evaluate whether the blinding of the assessment was successful, the Bang's method and James's method

were applied. After the post-assessment, independent evaluators were asked, "Which treatment do you think the participant received?" The response options provided were "Guided ICBT," "UC," or "Don't know."

Bang's blinding index ranges from -1 to 1, where 0 indicates perfect blinding. A value of 1 indicates complete unblinding, while -1 suggests that all participants' treatment allocations were incorrectly guessed. If the one-sided confidence interval excludes 0, the study is considered to have insufficient blinding.

Additionally, the James blinding index was calculated to provide further insight into the success of blinding.

The James index is a continuous measure ranging from 0 to 1, where a score of 0.5 indicates perfect blinding.

Higher values suggest a greater deviation from perfect blinding. Confidence intervals for the James index were also calculated to assess the adequacy of blinding.

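### Evaluators guess the arm only after measuring the outcome, so the rule that a Bang interval excluding 0 means insufficient blinding cannot separate unblinding from efficacy

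*Protocol*

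**What the plan says.** Section 6.5 places the guess after the outcome has been taken: "After the post-assessment, independent evaluators were asked, 'Which treatment do you think the participant received". Three answers are allowed: "The response options provided were 'Guided ICBT,' 'UC,' or 'Don't know". The reference value is fixed ("Bang's blinding index ranges from -1 to 1, where 0 indicates perfect blinding") and so is the conclusion to be drawn: "If the one-sided confidence interval excludes 0, the study is considered to have insufficient blinding". The James index is added from the same guesses.

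Section 5.6.3 shows what the evaluators know by then. "The independent assessor team at the University of Fukui measures the primary outcome via telephone", and the outcome "is assessed at baseline and 12 weeks post-intervention". The comparator is a waitlist on usual care (section 5.2), and section 6.6 plans for a large difference: "Assuming an expected effect size of 0.9 for this study".

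The protocol mentions no guess taken before the outcome call, no question on the reason for the guess, no adjustment for outcome, and no caution that correct guesses may come from efficacy. It does not state the confidence level of the one-sided interval, or whether one arm or both must fail.

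**The concern.** The rule tests the index against 0. Before any outcome is seen, 0 is the right reference for a blinded evaluator. After the call it is not: an evaluator who has just heard a low episode count can reasonably lean towards the active arm, and one who has heard a high count towards the waitlist. If treatment works, such guesses are right more often than chance although nobody has disclosed anything.

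This matters because participants know their arm and the primary outcome is what they report by telephone. The blinded evaluator is the main safeguard against biased measurement, and disclosure during the call is the obvious threat to it. Under the present rule, a failed check could mean disclosure or simply a treatment that works, and the three answer options leave no way to tell which. A trial that succeeds could be labelled inadequately blinded for that reason alone.

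**Working it through.** **Inputs from the protocol.** d = 0.9, two-sided 0.05, 80% power, 21 per group, and 30 per group after 30% dropout (section 6.6). Null value 0 and failure when the one-sided interval excludes 0 (section 6.5).

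**Assumptions, not in the protocol.** One-sided 95% interval; normal outcomes with equal variance; guesses split at the midpoint between the arms; no disclosure; no Don't know answers unless stated.

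**1. The protocol's own sample size.** Exact two-sample t-test power at d = 0.9 is 0.792 for n = 20 and 0.812 for n = 21, so 21 is reproduced. With dropout, 21 / (1 − 0.30) = 30, also reproduced. Guesses are made only after the post-assessment, so n = 21 applies if the expected dropout occurs and n = 30 if there is none.

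**2. Bang's index from the outcome alone.** If every guess follows the outcome, P(correct) = Φ(d/2) = Φ(0.45) = 0.674. With no Don't know answers the index is 2 × 0.674 − 1 ≈ 0.35 in each arm, although no allocation has leaked.

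**3. When the rule declares failure.** It does so when BI − 1.645 × √((1 − BI²)/n) > 0.
- n = 21: 14 correct gives BI = 0.333 and a bound of −0.005 (passes); 15 correct gives BI = 0.429 and a bound of 0.104 (fails).
- n = 30: 19 correct gives BI = 0.267 and a bound of −0.023 (passes); 20 correct gives BI = 0.333 and a bound of 0.050 (fails).

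The thresholds are therefore 15 of 21 and 20 of 30.

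**4. Probability of failure in a given arm with no disclosure.** Let q be the share of guesses that follow the outcome, the rest being coin flips: P(correct) = q × 0.674 + (1 − q) × 0.5. The last two columns are binomial probabilities of reaching the threshold.

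| Scenario | P(correct) | Bang index | n = 21 | n = 30 |
|---|---|---|---|---|
| d = 0 | 0.500 | 0 | 0.04 | 0.05 |
| d = 0.9, q = 0.25 | 0.543 | 0.09 | 0.09 | 0.12 |
| d = 0.9, q = 0.5 | 0.587 | 0.17 | 0.17 | 0.24 |
| d = 0.9, q = 1 | 0.674 | 0.35 | 0.45 | 0.62 |

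**5. Sensitivity at d = 0.9, q = 1.**
- With a one-sided 97.5% interval the figures are 0.45 (n = 21, where the threshold stays at 15) and 0.46 (n = 30).
- If evaluators answer Don't know for the middle 25% to 50% of outcomes, they are 0.59 to 0.60 (n = 21) and 0.71 to 0.73 (n = 30).
- If failure in either arm counts and the arms are independent, 1 − (1 − a)² gives 0.69 and 0.85. The protocol does not say that either arm suffices.

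**6. Does the check respond to disclosure?** Take d = 0, a share s of allocations disclosed and the rest coin flips, so P(correct) = s + (1 − s)/2.
- s = 0.3: P(correct) = 0.65; failure per arm 0.36 (n = 21) or 0.51 (n = 30).
- s = 0.5: P(correct) = 0.75; failure per arm 0.74 or 0.89.

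It does respond. Comparing steps 4 and 6 shows the difficulty: full reliance on the outcome with no disclosure (index 0.35) looks much the same as 30% disclosure with no effect (index 2 × 0.65 − 1 = 0.30).

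**The case against.** The strongest reply has four parts.

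- **The check is descriptive.** Nothing in sections 6.1 to 6.4 makes the primary analysis, its significance or an analysis set depend on it, and the James index is reported alongside. This stands and limits the harm to interpretation. The James index does not repair the point, because it rests on the same post-outcome guesses.
- **The size depends on evaluator behaviour that the protocol does not describe.** This stands. Pure outcome-based guessing with a known midpoint is an upper scenario, and the outcomes are episode counts rather than normal variables. The direction does not depend on these details: every scenario computed with a real effect gives a failure rate above that at d = 0.
- **Asking at the end is a recognised choice, and a reason item could sit on a form we have not seen.** That is fair as to the form. But the protocol itself states both the rule and its reading, so the reading is not something left to another document.
- **A new question may come too late.** Section 6.5 is written in the past tense and section 9 lists data collection as complete on 30 November 2024. This stands and shapes the fix.

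A reader might infer several stronger points that the documents do not support. One is that any above-chance guessing fails: the rule needs 15 of 21 or 20 of 30 correct. Another is that a working treatment will usually fail: even with full reliance the per-arm figure at n = 21 is 0.45, and with half reliance it is 0.17. A third is that the check cannot detect disclosure or passes ineffective treatments regardless: step 6 shows that it does react to disclosure and only fails to identify the cause. A fourth is that the evaluator compares with a known baseline count: section 5.6.3 says that a team measures both time points, not that one evaluator sees both. The calculation does not need this.

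**Conclusion.** The point holds as a flaw in a stated decision rule. Because the guess follows the outcome, a one-sided interval excluding 0 does not establish insufficient blinding when the treatment has an effect. At d = 0.9 and without disclosure, the false-failure probability per arm ranges from 0.09 (a quarter of guesses follow the outcome, n = 21) to 0.62 (all do, n = 30), against 0.04 to 0.05 with no effect. Confidence is high in the direction and modest in the size, which rests on unknown reliance on the outcome, an assumed 95% level, normal outcomes and no Don't know answers. The consequence is a possibly wrong conclusion about blinding; the estimate and test of the primary outcome are untouched. It should be corrected, but it is not critical to the trial's validity.

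**What to change.** In section 6.5:

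1. Delete the sentence that turns an interval excluding 0 into a finding of insufficient blinding.
2. Report Bang's index by arm with its confidence interval, and the James index, as descriptive results.
3. State that a Bang index above 0, obtained after the outcome is known, may reflect efficacy as well as unblinding, and draw no verdict from it alone.

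This needs no new data and can be done at reporting. The cost is a few reworded sentences and the loss of a pass/fail statement that the design cannot support.

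If any assessments remain, also record the main reason for each guess (disclosure by the participant, another study cue, change in symptoms, pure guess) and log any disclosure during the call. The small downside is that the reasons are self-reported by the evaluators. For calls already made this information cannot be recovered, and items 1 to 3 are then the whole fix.
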